## Abstract

**Background:**

Preeclampsia (PE) and intrauterine growth restriction (IUGR) are 2 major pregnancy complications due to abnormal placental vasculogenesis. Data on whole fetoplacental vasculature are still missing; hence, these pathologies are not well understood. Ex vivo magnetic resonance imaging (MRI) angiography has been developed to characterize the human placental vasculature by injecting a contrast agent within the umbilical cord.

**Objective:**

The primary objective of this study is to compare the placental vascular architecture between normal and pathological pregnancies. This study’s secondary objectives are to (1) compare texture features on MRI between groups (normal and pathological), (2) quantitatively compare the vascular architecture between both pathological groups (pathological IUGR, and pathological PE), (3) evaluate the quality of the histological examination in injected placentas, and (4) compare vascularization indices to histological characteristics.

**Methods:**

This is a prospective controlled study. We expect to include 100 placentas: 40 from normal pregnancies and 60 from pathological pregnancies (30 for IUGR and 30 for PE). Ex vivo MR image acquisition will be performed shortly after delivery and with preparation by injection of a contrast agent in the umbilical cord. The vascular architecture will be quantitatively described by vascularization indices measured from ex vivo MRI angiography data. Comparisons of vascularization indices and texture features in accordance with the group and within comparable gestational age will be also performed. After MR image acquisition, placental histopathological analysis will be performed.

**Results:**

The enrollment of women began in November 2019. In view of the recruitment capacity of our institution and the availability of the MRI, recruitment should be completed by March 2022. As of November 2021, we enrolled 70% of the intended study population.

**Conclusions:**

This study protocol aims to provide information about the fetal side of placental vascular architecture in normal and pathological placenta through MRI.

**Trial Registration:**

Clinicaltrials.gov NCT04389099; https://clinicaltrials.gov/ct2/show/NCT04389099

**International Registered Report Identifier (IRRID):**

DERR1-10.2196/35051

## Introduction

Placental dysfunction is a major cause of intrauterine growth restriction (IUGR) or preeclampsia (PE) and is responsible for maternofetal mortality and morbidity such as fetal death, preterm delivery, minor cognitive deficits, school problems, and metabolic syndrome in adulthood [1-3]. Normal placental development is an essential prerequisite for efficient placental function followed by fetal growth. Placental dysfunction is primarily due to a deficient remodeling of the spiral arteries in the myometrium during the first trimester [4]. These remodeling disorder leads to abnormal placental development with morphological and functional alteration of the placenta. The exploration of these alterations, functional and morphological, is important to not only understand the pathophysiology of IUGR and PE but also for screening or diagnostic techniques to improve antenatal care. Imaging tools are particularly suitable for this exploration.

As a consequence, some teams work on in vivo exploration of placental function using magnetic resonance imaging (MRI) or ultrasound imaging [5-7]. However, in vivo imaging has the disadvantage of having major difficulty in differentiating between the maternal and fetal sides, except for very advanced MRI techniques (DECIDE) for contrast-enhanced ultrasound imaging, which allows for the exploration of exclusively the maternal side and for MRI with gadolinium injection but is not allowed during pregnancy [8,9]. Besides, ex vivo studies seem to offer unique opportunities to explore placental physiology even outside the womb, where the placenta’s normal state is modified [10]. Two main tools have been described: ex vivo microcomputed tomography (micro-CT) and ex vivo MRI [11-13]. Regarding ex vivo micro-CT, Junaid et al [11] published a comparative analysis of placental vascularization between IUGR and normal placentas and showed a significant decrease in vessel length in IUGR placentas compared to normal ones.

Regarding ex vivo MRI, several studies described an MRI-compatible perfusion chamber allowing the exploration of dynamic placental perfusion during MRI scanning [14,15]. Ex vivo MRI could also be used to explore placental function.

Other studies have described a protocol for ex vivo angiography of the fetal vessels, including Link et al [16] and Chen et al [17]. The described technique allows for imaging of the architecture of the whole fresh human placental vascular tree by injection of oil in the umbilical cord vessels. This protocol can reveal up to the sixth level of placental vascularization at a submillimeter quasi-isotropic resolution [17]. Link et al [16] recently compared IUGR and normal placental vascular trees using ex vivo angiography [16]. The main limitation of this work is that the understanding of placental structure and vasculature at different gestational stages is limited [18,19].

The main objective of our study is to compare the vascular architecture of the placenta in normal and pathological pregnancies; for example, PE and intrauterine growth restriction. Our secondary objectives are to (1) compare texture features on MRI between groups (normal and pathological), (2) quantitatively compare the vascular architecture between both pathological groups (pathological IUGR and pathological PE), (3) evaluate the quality of the histological examination in injected placentas, and (4) compare vascularization indices to histological analysis.

## Methods

### Trial Design

The MRI Angiography of Physiological and Pathological Pregnancy Placentas *Ex vivo* (MAPLE) protocol is a prospective, monocentric (Maternité du Centre Hospitalier Régional Universitaire [CHRU] de Nancy, France), open, controlled, nonrandomized pilot study conducted at CHRU de Nancy. Figure 1 presents the study flowchart.

**Figure 1 figure1:**
[figure not shown]
Study flowchart. GW: gestational week; IUGR: intrauterine growth restriction; MRI: magnetic resonance imaging.

### Study Population

Enrolled women will be distributed into 3 groups (normal, IUGR, and PE) in accordance with their pregnancy status. The participants in this study are pregnant women in their third trimester in order for us to obtain comparable gestational ages between groups. Textbox 1 presents the inclusion and exclusion criteria. IUGR is defined as a birth weight less than the third percentile of the French growth curve (Association des Utilisateurs de Dossiers Informatisés en Pédiatrie, Obstétrique et Gynécologie, Lyon, France). PE is defined as a systolic blood pressure of ≥140 mm Hg and a diastolic blood pressure of ≥90 mm Hg associated with proteinuria of >300 mg per 24 hours after 20 weeks of gestation. Before inclusion, women will be informed of the aim, procedures, and predictable risks of the study (no identified clinical risk) by the investigator. Patients’ medical history, including smoking and obstetric history, will be collected. Medical information on the current pregnancy will also be collected (Textbox 2).

Inclusion and exclusion criteria.
**Inclusion criteria:**
Already received complete information about the study and do not express any opposition to the use of their dataMandatory enrollment in a social security planGestational age of >25 weeks (and until at term)Having undergone either natural or Cesarean delivery and whose placenta is naturally completely separatedFor the normal group:Normal fetal weight (between the 10th and 95th percentile for age)No intrauterine growth restriction (IUGR) or preeclampsia (PE) suspected or confirmedNo Doppler (fetal and umbilical) abnormalityFor the pathological group:Subgroup IUGR: IUGR defined by a fetal estimated weight of less than the third percentile of the antenatal curve, and confirmed in the postnatal stage; absence of associated PESubgroup PE: clinical diagnosis of PE (high blood pressure associated with significative proteinuria); absence of associated IUGR
**Exclusion criteria:**
Younger than 18 yearsNewborn with congenital disease (either suspected at birth or already diagnosed)Presence of only one umbilical arteryPresence of a maternal pathology: gestational diabetes, pre-existing autoimmune diseases, or cancerDo not speak French or inability to understand the given information of the studyManual deliveryIncomplete placentaPerson referred to articles L.1126-6 and L-1126-8 of the public health code

Data collected.
**Habitus:**
Smoking and addictionsDrug consumption
**Obstetric data:**
Gestational age, parity, and birth weight
**Clinical data:**
BMI and ageFor preeclampsia: proteinuria, blood pressure (systolic and diastolic), and complicationsFor intrauterine growth restriction: ultrasound data (biometry, umbilical artery Doppler, and estimated fetal weight)
**Magnetic resonance imaging data:**
Morphological images of the placenta, vascularization indices, and texture indices
**Histological data:**
Placental analysis (weight and morphological analysis)

### Placenta Preparation for Perfusion

All human placentas will be immediately collected and prepared for acquisition after natural vaginal delivery or Cesarean delivery to reduce the occurrence of blood clotting. The preparation procedure was based on Rasmussen’s procedure modified by Chen et al [17] to fit our requirements [20]. First, a gross macroscopic examination of the placenta will be performed as described by the Amsterdam Placental Workshop Group Consensus, including placental weight, dimensions, and descriptions of the umbilical cord, membranes, and lesions [21]. Next, fresh placentas will be placed in a water bath at 37 °C during preparation. The chorion and amnion will be trimmed and removed. The umbilical cord will be severed at a 5-cm length to its placental insertion point. Umbilical vessels will be catheterized. The placental vascular bed will be slowly rinsed with a water-based solution through catheters fixed to the artery. The wash will be stopped when the reflux from the vein catheter becomes completely clear. The contrast agent (B-oil for rotary vane pumps, Vacubraand) will be slowly injected through the umbilical arteries until outflow of the contrast agent in the vein is observed, to ensure microvessel filling. The arteries and veins need to be closed well at their entry points. The overall preparation time is 1 hour. The sealed cord will be placed within a plastic tube supporter (the residual umbilical cord part), which was dedicatedly designed and printed with a 3D printer (Figure 2). Within this holder, the umbilical cord was tightly attached and not compressed so that the primary level of the vein and artery vessel trees can be distinguished in the MR data for the subsequent vessel tree extraction algorithm, especially to be able to separate arteries and veins. After preparation, the placenta will be stored in a refrigerator at 4 °C.

**Figure 2 figure2:**
[figure not shown]
Placenta prepared for magnetic resonance imaging. The placental vascular tree is filled with oil. The sealed cord is placed within a plastic tube supporter designed and printed with a 3D printer.

### MR Image Acquisition

Prepared placentas will be taken out from the refrigerator and placed in the MR room for approximately 30 minutes before MR image acquisition in order to ensure a steady temperature during the whole acquisition procedure. It will be placed on top of a flat platform appropriate for placental size: one with a diameter of 22 cm, the other with a diameter of 22.5 cm. Both can be fitted inside a 20-channel head coil. Therefore, the placenta is well placed at the isocenter of the MRI bore so that the homogeneity of the magnetic field can be maximumly satisfied. The imaging protocol has been tuned and set up on a 3T Prisma Siemens MR scanner. A 3D Flash sequence is employed to acquire the data. The relevant parameters are 0.4 × 0.4 × 0.4 mm^3^, TR/TE 8/3.5 milliseconds, 512×512 acquisition matrix, bandwidth of 390 Hz, and 14 NEX. The field of view and number of slices can vary from placenta to placenta, but all will be adjusted to achieve the aforementioned acquisition parameters, especially the isotropic resolution. Neither parallel imaging nor partial Fourier acquisition strategies have been adopted. The mean overall acquisition time was 1 hour 40 minutes. After MR image acquisition, the placenta will be immediately sent back to the pathology laboratory for histological processing, being always maintained at 4 °C.

### Pathological Examination

After MR image acquisition, the entire placenta will be fixed in a 4% formaldehyde solution for approximately 1 month. Random samples of cord, membranes, and placental parenchyma will be submitted (4 blocks as a minimum and 1 block for each type of lesion) in accordance with the recommendations of the Amsterdam Consensus Statement and be subjected to histopathological evaluation [21]. Once the tissue block is embedded in paraffin wax, a 6-µm vertical section containing the entire thickness of the placenta will be taken and mounted for staining with hematoxylin and eosin.

Certified pathologists will read slides to establish a histopathological diagnosis. Gross and histological lesions of fetal and maternal vascular malperfusion will be reported. Fetal vascular malperfusion (FVM) will be classified as global/partial or segmental/complete, and high-grade FVM will be also reported [22,23]. Finding of maternal vascular malperfusion (MVM) we be classified into villous changes (infarcts, retroplacental hematoma, accelerated villous maturation, and distal villous hypoplasia) and vascular lesions (acute atherosis, persistent muscularization of basal plate arterioles, basal decidual vessel thrombosis, and mural hypertrophy of membrane arterioles) [22]. MVM will be graded as global/partial or segmental/complete [23].

### MR Image Analysis

All the placental data will be archived and managed by a local research image management system ArchiMed. A MATLAB program has already been developed to segment the acquired placenta data and extract the vessel tree structure [17]. Owing to the good contrast-to-noise ratio and signal-to-noise ratio of the MR images, a simple thresholding is sufficient to delineate the vessel tree. A fast-marching algorithm will be used to quantitatively characterize the placenta’s vessel tree. Separation of the artery and vein tree structure will be achieved with a homemade software written in C++ as described by Kerrien et al [24]; the segmented placenta vessel data will be rendered in 3D, and its skeleton will be overlapped with its 3D model using this software. Morphological parameters including total vessel density, artery and vein density (per cm^3^), and tortuosity and bifurcation density (per cm^3^) will be calculated automatically or semiautomatically. Total vessel density is defined as the overall vessel density regardless of whether the vessel is an artery or vein. It is calculated as the vessel voxel volume divided by the whole placenta volume, while artery and vein vessel density are defined as artery and vein volume divided by whole placenta volume, respectively. The 3-vessel density will be calculated automatically by the software. Calculation of tortuosity and bifurcation density are computed semiautomatically as the branching of the vessel network and bifurcations need to be checked by observers. Tortuosity is defined as the curvilinear distance and Euclidean distance between the starting and the end of a vessel path (in this case, a vessel branch) [24]. Bifurcation density is defined as the number of detected bifurcations divided by the placental volume. Radiomics features, as described by Vallières et al [25], will also be extracted to quantify the differences among the 3 groups of placentas [25]. The quantitative parameters will be described by their mean (SD), median, maximum and minimum, and n (%) values. Mean values between groups will be compared using the Student *t* test or Mann-Whitney test, unpaired in accordance with whether the data are normally distributed, depending the type of data. Linear regression models will be used to test the group and the effect of gestational age on the parameters considered.

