### Outcomes

The primary outcome will be the vascular architecture, described by vascularization indices (total vascular density, arterial and venous density in cm^3^, tortuosity index, and branching index) measured from ex vivo MRI in both groups (physiology and pathology).

The secondary outcome measures are the following:

Secondary objective 1: measurement of texture indices as established by Vallières et al [25].Secondary objective 2: measurement of vascularization indices and texture based on the participant group.Secondary objective 3: number of placentas with an appropriate histological quality to be examined microscopically.Secondary objective 4: statistical comparison between vascularization indices achieved through MRI and histological evaluation (presence or absence of FVM, presence of absence of MVM, if present: grading of the lesions).

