## Discussion

This study aims to evaluate whole human placental vasculature using ex vivo MRI in a normal and pathological population. We hypothesize that the placental vascular tree is altered in case of IUGR or PE compared to normal pregnancy. Our study data will provide information about uteroplacental physiology and pathophysiology by the exploration of the fetal placental side.

To our knowledge, this is the first prospective, comparative, controlled study comparing the architecture of the placental vascular tree between normal and pathological pregnancies at the same gestational age.

The groups have been selected strictly on the basis of gestational age and neonate size at birth to assess the comparison. This technique has been previously evaluated in a pilot study carried out by our team; however, only the fetal side can be analyzed with this technique.

The strength of our study is the large sample size compared to that in other studies and the control of confounding factors such as gestational age. Furthermore, our team comprises both obstetrics experts ([name]), who ensured the relevance of definitions of pathologies, and imaging experts with research engineers ([name]).

The main limitation of this study is the lack of clinical applicability of this technique. A promising recent study demonstrated the possibility to image the placental vascular tree in vivo [9]. Our results, combined with this technique, could provide to parents and obstetricians useful information during pregnancy. This trial is in accordance with the Standard Protocol Items: Recommendations for Interventional Trials checklist.

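### Two of the five primary indices depend on observer checks in a study declared open, and nothing withholds group from those observers

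*Protocol article*

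**What the plan says.** The Outcomes section of the protocol article defines the primary outcome by five vascularization indices: total, arterial and venous density, tortuosity, and branching. The last two appear there as "tortuosity index, and branching index) measured from ex vivo MRI in both groups (physiology and pathology".

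The MR Image Analysis section separates these indices by how they are obtained. Of the densities it says "The 3-vessel density will be calculated automatically by the software". Of the other two it says "tortuosity and bifurcation density are computed semiautomatically as the branching of the vessel network and bifurcations need to be checked by observers". Bifurcation density is the number of bifurcations found divided by placental volume, and tortuosity is computed along each vessel branch.

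Trial Design calls the work an "open, controlled, nonrandomized pilot study". The Discussion states the expectation: "We hypothesize that the placental vascular tree is altered in case of IUGR or PE compared to normal pregnancy".

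Two sections deal with coding. Data Collection and Management has the MRI data anonymized for secure transfer and archiving. Patient Data Protection has specimens and case report forms labelled with initials and an inclusion-order number. Neither says that group is hidden from the people who check the vessel trees.

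**The concern.** A count of bifurcations changes when an observer decides that one is real or spurious, and tortuosity changes with the branches on which it is computed. Both quantities enter the primary comparison. An observer who knows that a placenta comes from an IUGR or PE pregnancy, and who expects an altered tree there, may resolve doubtful branches differently from the way they would in a normal placenta.

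Such a shift is systematic, so a larger sample does not average it out. The planned regression on group and gestational age does not remove it either: the shift follows the group label and is absorbed into the group coefficient. At stake is whether a difference in tortuosity or branching can be read as biology.

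**Working it through.** **Which indices are exposed**

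| Primary index (Outcomes) | How obtained (MR Image Analysis) | Observer judgement stated? |
|---|---|---|
| Total density | automatic | no |
| Arterial density | automatic | no |
| Venous density | automatic | no |
| Tortuosity | semiautomatic | yes |
| Branching | semiautomatic | yes |

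Two of five are exposed. This takes the branching index in Outcomes to be the bifurcation density in MR Image Analysis. The names differ, but no other branching measure is defined.

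**Is group concealed anywhere?** Trial Design says open. The anonymization and the ID labels concern identity. No other section describes what the observers know.

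**How much could a shift matter?** The article has no figure to reproduce: Sample Size Consideration gives group sizes but no alpha, power, SD or effect size. What follows is an illustration.

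- From the article: 40 normal and 60 pathological placentas (30 IUGR, 30 PE), compared by Student *t* or Mann-Whitney test.
- Assumed: two-sided alpha 0.05, no true difference, and a reading shift of b SD in one consistent direction in the pathological group.

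Standard error in SD units: SE = √(1/40 + 1/60) = √0.04167 = 0.204.

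Probability of a significant result, normal approximation: P = 1 − Φ(1.96 − b/SE) + Φ(−1.96 − b/SE).

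For b = 0.2: b/SE = 0.98, so P = 1 − Φ(0.98) + Φ(−2.94) = 0.1635 + 0.0016 = 0.165.

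For normal against one pathological subgroup, SE = √(1/40 + 1/30) = 0.242.

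| Assumed shift b (SD) | 40 v 60 | 40 v 30 |
|---|---|---|
| 0 | 5.0% | 5.0% |
| 0.1 | 7.8% | 7.0% |
| 0.2 | 16.5% | 13.1% |
| 0.3 | 31.2% | 23.7% |
| 0.4 | 50.0% | 38.1% |
| 0.5 | 68.8% | 54.4% |

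The noncentral *t* distribution gives 7.7%, 16.3% and 30.7% for 40 v 60 at 0.1, 0.2 and 0.3 SD, so the approximation is adequate. At 40 v 60, an observed difference of 1.96 × 0.204 = 0.40 SD is enough for significance.

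**The case against.** The strongest reply is that this is a condensed article. It nowhere says that observers know the group. The word open labels the study as a whole, reading procedures often sit in the full protocol, and coded, anonymized images are compatible with masked reading.

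Part of this stands: the absence of masking is inferred from the open label plus silence, and the full protocol may say more. It does not dispose of the point. The article commits itself to an open design and to observer-checked primary indices. Masking of those who assess a primary outcome is a design feature that a protocol article would normally report. If the image database already hides group, one sentence would settle the matter.

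It is also fair to object that the assumed shifts have no anchor in the documents. The percentages show how the test responds to a given shift. They are not evidence that one occurs.

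A reader might infer more than the text supports:

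- **That the densities are exposed too, through an operator-set threshold.** The article says only that "a simple thresholding is sufficient to delineate the vessel tree". It does not say that anyone sets the threshold placenta by placenta, and it calls the density calculation automatic.
- **That observers edit the trees by hand.** The text speaks of checking within a semiautomatic computation. A check that could change nothing would serve no purpose, but the extent of any change is not described.
- **That the bias has a known direction.** The stated hypothesis is alteration, with no sign given for tortuosity or branching. The illustration needs a consistent direction, which is an assumption.
- **That the damage would be permanent.** The images are archived, so a masked re-read is possible.
- **That pathologists know the MRI indices when they grade lesions.** The article says "Certified pathologists will read slides to establish a histopathological diagnosis" and nothing about access to the indices. That worry rests on silence alone.

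**Conclusion.** The point holds for tortuosity and branching, two of the five primary indices. As written, the plan leaves both open to reader bias: observers check the features that determine them, the study is open, a group difference is expected, and no section withholds group.

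The size of any bias is unknown. Under the assumptions stated (no true effect, two-sided alpha 0.05, a consistent shift, 40 v 60), shifts of 0.1 to 0.3 SD would raise the false-positive rate from 5% to between about 8% and 31% for each index affected. The conclusion does not depend on any particular value in that range.

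It does depend on two readings: that the open label, with nothing to qualify it, covers image reading, and that the branching index is the bifurcation density. The sponsor should make the change. The point does not call the three densities into question and does not invalidate the study.

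**What to change.** State in MR Image Analysis that:

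- observers check branching and bifurcations on images carrying only a study code, in random order;
- group, gestational age, birth weight and clinical data are withheld from them (birth weight matters because the article defines IUGR by it);
- the group key is joined only after both indices are final for all placentas;
- any scans already checked with group known are re-presented in this way to the same observers.

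The article reports 70% enrolment by November 2021 but does not say how many scans had been checked, so the amount of repeat work cannot be estimated from it. The change needs a coding step in the existing image archive and some repeat checking. It needs no new participants, scans or readers. Its limit is that placental size remains visible and may hint at group, so masking reduces the risk without removing it.

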### Statistical Analysis

Quantitative data will be described by their mean (SD), median, and maximum and minimum values. Qualitative data will be expressed as n (%) values. Between-group comparisons will be performed using the Student *t* test or the Mann-Whitney test, matched or unmatched, depending on the type of data. The chi-square test or the Fisher exact test will be used to compare the qualitative data between groups. The analyses will be performed with R software (R Foundation for Statistical Computing). No intermediary analysis is intended. The analyses will be performed on a per-protocol basis.

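### The protocol states the texture comparison inconsistently and does not say which contrast or test decides secondary objective 1, so chance texture differences arise more often than the nominal rate

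*Protocol article*

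**What the plan says.** The protocol article describes the texture (radiomics) comparison in several places.

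- **Abstract (Objective) and Introduction.** Secondary objective 1 is to "compare texture features on MRI between groups (normal and pathological"), so two groups. Secondary objective 2 is to "quantitatively compare the vascular architecture between both pathological groups"; texture is not part of it.
- **MR Image Analysis.** The radiomics features "will also be extracted to quantify the differences among the 3 groups of placentas", so three groups.
- **Outcomes.** The outcome for objective 1 is the "measurement of texture indices as established by" a cited source; the features are neither listed nor counted. The outcome for objective 2 is the "measurement of vascularization indices and texture based on the participant group", which brings texture into an objective that does not mention it.
- **Tests.** Statistical Analysis states: "Between-group comparisons will be performed using the Student *t* test or the Mann-Whitney test, matched or unmatched, depending on the type of data". MR Image Analysis names the same two tests and adds: "Linear regression models will be used to test the group and the effect of gestational age on the parameters considered".

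No section states a significance level, or says whether the regression or the two-sample test takes precedence. Trial Design calls the study a pilot, and Sample Size Consideration calls it exploratory.

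**The concern.** An analyst following this text could give each texture feature one contrast (normal against pooled pathology), two (adding IUGR against PE) or the three pairwise contrasts. Each could be run as a two-sample test or as a regression term with gestational age. These choices can disagree for the same feature, and the text does not say which result answers objective 1.

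Texture sets usually hold many features. With several routes per feature and no deciding contrast, a chance difference in about 100 placentas could be reported as a mark of disease. The issue is confined to the secondary texture outcomes; the primary vascular indices are not affected.

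**Working it through.** **No plan figure to reproduce.** The sample size is 40 + 30 + 30 = 100, set by a minimum of 30 per group. No alpha, power, effect size or error rate lies behind it.

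**Step 1: the statements side by side.**

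| Section | Groups compared on texture |
|---|---|
| Abstract (Objective); Introduction, objective 1 | normal vs pathological |
| Abstract (Objective); Introduction, objective 2 | none (vascular architecture only) |
| MR Image Analysis | among three groups |
| Outcomes, objective 2 | texture by participant group |

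The first and third rows differ for the same features. The second and fourth differ on whether objective 2 includes texture.

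**Step 2: the contrasts are not interchangeable.** Let a feature shift by *d* in IUGR and by *e* in PE, relative to normal. With 30 placentas in each subgroup the pooled shift is (30*d* + 30*e*)/60 = (*d* + *e*)/2. If only IUGR is affected (*e* = 0), pooling halves the shift. If the shifts are opposite (*e* = −*d*), pooling removes it. The two-group and three-group readings can therefore give different answers.

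**Step 3: error rate on the single contrast of objective 1.** Inputs from the document: 40 normal and 60 pathological. Assumed, because not stated: two-sided 0.05 per feature, no adjustment, *m* = 10, 20 or 40 features, each tested separately, and a common correlation between features.

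For independent features the chance of at least one false positive is 1 − 0.95^*m*: 0.401 (*m* = 10), 0.642 (*m* = 20), 0.871 (*m* = 40). It first passes one half at *m* = 14 (1 − 0.95^14 = 0.512). The expected number of false positives is 0.05*m* = 0.5, 1 and 2, whatever the correlation.

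Correlation lowers the chance of any false positive. Simulated under the null, with z-tests (200,000 runs) and with t tests at 40 vs 60 (2,000 runs):

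| Correlation | Test | *m* = 10 | *m* = 20 | *m* = 40 |
|---|---|---|---|---|
| 0 | z | 0.402 | 0.641 | 0.873 |
| 0 | t | 0.394 | 0.631 | 0.872 |
| 0.5 | z | 0.288 | 0.420 | 0.571 |
| 0.5 | t | 0.304 | 0.426 | 0.587 |
| 0.8 | t | 0.170 | 0.234 | 0.294 |
| 0.9 | z | 0.128 | 0.155 | 0.184 |
| 0.9 | t | 0.117 | 0.142 | 0.176 |

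The two simulations agree within simulation error; for the smallest cell the standard error at 2,000 runs is √(0.117 × 0.883/2000) = 0.007. Every cell exceeds 0.05, but many lie below one half.

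**Step 4: what adjustment could cost.** Benjamini-Hochberg rejects at least everything that Bonferroni rejects at the same level, so Bonferroni gives the worst case. Take an illustrative difference of 0.58 SD, 40 vs 60, normal approximation. The standard error is √(1/40 + 1/60) = 0.204 SD, and 0.58/0.204 = 2.84.

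- At 0.05: Φ(2.84 − 1.96) = 0.81.
- At 0.05/40 = 0.00125: Φ(2.84 − 3.23) = 0.35.

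Power for such a feature would therefore fall from about 81% to no lower than about 35%.

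**The case against.** **The missing multiplicity rule.** This is a journal article about a self-declared exploratory pilot. A feature list and a multiplicity rule for a secondary imaging outcome are commonly left to an analysis plan, which is not shown. This stands: the absence of such a rule is not, alone, a finding. What remains is the disagreement between sections, which brevity does not explain and which has to be settled before any adjustment can be defined. It is also true that no texture p-value is expressly labelled descriptive.

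**The contrast for objective 1 is stated.** Abstract and Introduction give it in the same terms, and the MR Image Analysis sentence may only explain why features are extracted. This is a fair reading and a good reason to keep that contrast. It does not remove the need to bring the other two sections into line.

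**Readings that go too far.** A reader might infer three things that the document does not support.

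- *That only two-group tests are planned, so a three-group question cannot be answered.* The planned regression could carry a three-level group factor. The gap is that its coding and priority are not given.
- *That three pairwise tests per feature are planned.* No section sets these out. If they were run, the simulated chance at correlation 0.5 would be about 0.56, 0.72 and 0.87 for 10, 20 and 40 features, but those figures describe an analysis the text permits, not one it specifies.
- *That a false texture finding is likely.* Alpha and feature count are not stated, separate testing of each feature is inferred from the general test sentence, and with 10 to 20 features at correlation 0.5 the chance is about 0.29 to 0.42.

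**Conclusion.** The point holds as an inconsistency with a moderate statistical consequence. The texture contrast differs between the objectives, MR Image Analysis and Outcomes, and the deciding test is not identified. If features are tested one at a time without adjustment, the chance of at least one false texture difference on the stated two-group contrast is about 0.13 to 0.87, depending on feature count and correlation. That is above 0.05 across the range examined, but whether it exceeds one half cannot be known from the document. The range rests on an assumed two-sided 0.05, 10 to 40 features, equal correlation between features and no true difference. This is a worthwhile, inexpensive improvement to a secondary objective of an exploratory study; it does not put the primary comparison in doubt.

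**What to change.** Before the texture data are analysed:

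1. Bring Abstract, Introduction, MR Image Analysis and Outcomes into agreement, with normal vs pathological as the one deciding texture contrast for objective 1.
2. Test that contrast for each feature with the linear regression on group and gestational age already planned in MR Image Analysis, with group coded as two levels. State that this model, and not the two-sample test, decides. This retains gestational age, which the Discussion names as a controlled confounder; an omnibus three-group test without it would not.
3. Report Benjamini-Hochberg-adjusted p-values at a 5% false discovery rate over all extracted features, beside the raw p-values, and give the number of features tested with the number declared different.
4. Label the three-group and IUGR-vs-PE texture comparisons as exploratory. In Outcomes, either remove texture from objective 2 or mark it as exploratory there.

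The cost is a few sentences and one line of R code, with no additional placentas. The downside is that fewer individual features will be declared different.
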